### Sociodemographic and clinical data

Sociodemographic data (age, partner status, education, tobacco, alcohol and drug use), weight, medical history, parity status and, in case of prior pregnancy, pregnancy history and outcome, were documented at enrolment. A medical exam was conducted at the same time point that included body mass index, blood pressure (BP), and haemoglobin measurement, urine analysis, testing for HIV and other sexually transmitted diseases, assessment of pregnancy symptoms, and a dating ultrasound. Subsequent antenatal visits included determination of GA, recording of pregnancy symptoms since the prior visit, and testing for urine, haemoglobin, BP, heart rate, and weight. At delivery, medical conditions or medications during pregnancy and/or delivery, time of membrane rupture, delivery time, and birth outcome were documented. The foetus’s heart rate and fundal height were also assessed. Data also captured indications for provider-initiated delivery or caesarean section, postpartum complications, neonatal vital status, and Apgar score. Women and infants were seen at least once between six weeks to six months post-delivery. The infant was evaluated for any diseases and medications since birth, and evaluated for infant weight, head circumference, mid-upper arm circumference, temperature, heart and respiratory rates. The mother underwent a pelvic exam and was assessed for weight, BP, heart rate, temperature, and oedema.

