## DATA ANALYSIS AND DATA INTEGRATION

The analytical objectives of MOMI are to determine the omics signatures of each week of advancing GA (*i.e.* temporal pregnancy progression), the strength of association of each omics or other analytical platform with each APO through machine learning modelling (thereby identifying unique features of each APO phenotype), and how site-specific effects can be used to inform model generalisation. Analysis will proceed systematically from using risk signatures derived from a single platform to signatures identified through integration of multiple omics risk signatures, and from individual cohorts to cross-cohort integration. The integration of phenotypic metadata, including sociodemographics and clinical variables, will further enhance the understanding of biological mechanisms underlying APOs and improve prediction of APOs.

The structural heterogeneity across global cohorts presents a central analytical challenge that will be addressed by explicit methodological safeguards against batch effects, missingness, site heterogeneity, and overfitting. The MOMI analytical framework is built on a mature and extensively validated computational pipeline developed and applied across multiple large, multi-site pregnancy cohorts, including prior MOMI studies [17,19] and in subsequent multi-omic integration and machine-learning frameworks [15,18,20,21]. In these works, we have implemented harmonised preprocessing and quality control, explicit modelling of batch and site effects, and integration strategies that preserve biological signal while mitigating technical variation (*e.g.* empirical Bayes and factor-based normalisation, network-based integration, and multi-view latent variable models). Missing data are handled through a combination of modality-aware imputation and model architectures that accommodate partially observed samples, enabling inclusion of participants with incomplete data without introducing bias.

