For non-machine learning association analyses, we will use a prespecified covariate framework grounded in clinical relevance and established epidemiologic confounders, including maternal age, body mass index, parity, GA at sampling, and study site. These variables will be incorporated within mixed-effects or hierarchical regression models to appropriately account for cohort structure and site-level heterogeneity, with model specifications defined *a prior* to avoid data-driven overfitting. To control for false-positive findings across the large number of molecular features tested, we will apply false discovery rate correction within each omics layer and, where appropriate, across integrated analyses.

Although statistical harmonisation approaches such as ComBat are effective at reducing batch effects, they may inadvertently remove meaningful biological or population-level differences between sites. Therefore, our primary framework prioritises external validation across sites as the most conservative test of reproducibility and transportability. Rather than relying solely on post hoc harmonisation, our primary strategy is to evaluate robustness and generalisability directly. Specifically, we will train models on subsets of study sites and validate them on held-out sites. This design allows us to assess real-world performance under true site-level variation, including differences in GA assessment, biospecimen handling, and sociodemographic context. This cross-site training and validation framework ensures that identified signatures are not artifacts of a single cohort, platform, or operational pipeline, but instead reflect patterns that are stable across diverse populations. Only models and associations that replicate across sites will be interpreted as biologically meaningful, providing a principled basis for pooled analyses. As a complementary, secondary analysis, we will apply ComBat-based correction and mixed-effects modelling to quantify and compare the impact of site-level harmonisation. This layered approach allows us to rigorously test whether pooled analyses are justified, distinguish technical from biological sources of heterogeneity, and preserve interpretability, while maintaining statistical rigor across structurally heterogeneous cohorts.

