The computational pipeline employs dimensionality reduction and unsupervised clustering for sample classification, followed by statistical modelling to identify signatures associated with adverse outcomes while accounting for confounding factors. Longitudinal analysis characterises trajectories during normal pregnancy progression, providing essential context for understanding pathological changes. In parallel to the statistical approaches, machine learning will be applied to identify signatures with predictive value to enable the development of assays with diagnostic and prognostic value for the identification of APOs. This multi-layered analytical strategy aims to distinguish universal molecular signatures from population-specific variations. Pathway enrichment analysis is an essential step for interpreting the results of predictive models in biological terms, particularly when the aim is to understand the molecular mechanisms of distinct APOs. The different omics platforms will employ distinct pathway analysis tools, such as KEGG Pathway Database, Gene Ontology, STRING, MetaboAnalyst, and others [56-58]. Pathway enrichment will be conducted separately for each site and APO to ensure that the localised biological processes are accurately captured. To predict APOs of interest, machine learning techniques, specifically models based on eXtreme Gradient Boosting [59], a powerful and efficient implementation of gradient boosted decision trees, will be used. For each outcome, a distinct model will be constructed at various pregnancy stages to capture the static risk at that time point. One hundred bootstrap iterations will be performed during which a subset of the patients equal to the size of the full data set will be selected randomly with replacement. This method involves repeated random sampling to split the data into training and validation sets, thus providing a thorough assessment of model performance across various data subsets.

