To control for site imbalance in a multi-country cohort, all resampling procedures will be performed using stratified bootstrapping that preserves the joint distribution of site and outcome status. Specifically, bootstrap samples will be drawn within strata defined by study site and outcome (and, where relevant, by case-cohort membership), ensuring that each resample reflects the original cohort’s structural heterogeneity. This approach maintains appropriate representation of under-represented sites and rare outcomes in each iteration, preventing dominance by large sites and reducing bias in variance estimation and model stability assessments. Stratified resampling will be used consistently for uncertainty estimation, feature stability analyses, and performance evaluation, providing a more rigorous assessment of robustness in the presence of site imbalance. The GARBH-INi data will be utilised to validate data generated by the MOMI cohorts and, *vice versa*, GARBH-INi findings may be validated using the MOMI cohort data. The performance of these predictive models will be evaluated using area under the receiver operating characteristic and the area under the precision-recall curve, as well as prevalence of the case. Multi-site analysis is a critical component of model building, ensuring that the predictive models are robust and applicable across different populations and conditions.

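### The omics prediction models have no stated clinical-only comparator, and replication across sites cannot show that they add to data already collected at enrolment

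*Protocol article*

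**What the plan says.** All from the Protocol article; the section is Data analysis and data integration unless another is named.

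- **Build order.** "Analysis will proceed systematically from using risk signatures derived from a single platform to signatures identified through integration of multiple omics risk signatures". The role of clinical data comes in a separate sentence: "The integration of phenotypic metadata, including sociodemographics and clinical variables, will further enhance the understanding of biological mechanisms underlying APOs and improve prediction of APOs".
- **Two streams.** "In parallel to the statistical approaches, machine learning will be applied to identify signatures with predictive value". The prediction models are gradient-boosted trees, one per outcome at each of several pregnancy stages.
- **Metrics.** Performance is "evaluated using area under the receiver operating characteristic and the area under the precision-recall curve, as well as prevalence of the case". No comparator model and no measure of incremental value is named.
- **Adjustment.** "For non-machine learning association analyses, we will use a prespecified covariate framework", with covariates "including maternal age, body mass index, parity, GA at sampling, and study site". Nothing comparable is stated for the machine-learning models.
- **Acceptance.** Models are trained on some sites and validated on others, and only what replicates is read as biologically meaningful. The introduction goes further and makes reproducibility across sites the condition for calling a signature clinically as well as biologically meaningful.
- **Data at hand.** Under Sociodemographic and clinical data, "parity status and, in case of prior pregnancy, pregnancy history and outcome, were documented at enrolment". The enrolment examination also covered BMI, blood pressure, haemoglobin and HIV testing.

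**The concern.** The introduction aims at new risk assessment tools, the analysis section at assays with diagnostic and prognostic value, and the discussion at early detection in low- and middle-income settings. For those aims the deciding question is what an assay adds to history, BMI, blood pressure and haemoglobin, which the sites already record.

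Held-out-site validation protects against signatures that are artefacts of one cohort, platform or pipeline. It does not protect against a molecular proxy for a clinical risk factor that acts at every site, because the proxy replicates along with the factor.

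Preeclampsia shows how this could arise. The Data harmonisation section says that chronic hypertension could not be uniformly excluded at enrolment, and that severe blood pressure without proteinuria counts as preeclampsia whatever the earlier hypertension status. A molecular correlate of raised enrolment blood pressure could then predict preeclampsia across sites while repeating a reading already on file.

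**Working it through.** **1. The plan's own reference values (Table 2; 16 221 pregnancies).** Site counts are in the order Zambia, GAPPS Bangladesh, AMANHI Bangladesh, Pakistan, Tanzania.

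- Preterm birth: 223 + 384 + 366 + 372 + 242 = 1587; 1587/16 221 = 9.78%
- Preeclampsia: 85 + 35 + 7 + 39 + 124 = 290; 290/16 221 = 1.79%
- SGA: 434 + 936 + 1044 + 683 + 430 = 3527; 3527/16 221 = 21.74%
- Stillbirth: 62 + 25 + 21 + 31 + 29 = 168; 168/16 221 = 1.04%

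All four agree with Table 2. Prevalence is the AUPRC of a model with no skill. The article states no target AUROC, threshold or power for the prediction models.

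**2. A pure proxy (assumed inputs).** Let a clinical score C have AUROC a, normal with equal variance in cases and non-cases. Its shift is d = √2·Φ⁻¹(a). Let the omics score be M = ρC + √(1−ρ²)·noise, so that M says nothing about the outcome beyond C. Then AUROC(M) = Φ(ρd/√2). The article gives neither a nor ρ, so I show a range.

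- a = 0.65, ρ = 0.9: d = 0.545, ρd = 0.49, AUROC(M) = 0.636
- a = 0.70, ρ = 0.7: AUROC(M) = 0.643
- a from 0.60 to 0.75, ρ from 0.5 to 0.9: AUROC(M) from 0.55 to 0.73

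**3. Would the proxy look successful?** As a yardstick of my own, I take a two-sided 5% test of AUROC against 0.5 with the Hanley-McNeil standard error: SE² = [A(1−A) + (n₁−1)(Q₁−A²) + (n₀−1)(Q₂−A²)]/(n₁n₀), where Q₁ = A/(2−A) and Q₂ = 2A²/(1+A). The probability of success is Φ((A−0.5)/SE − 1.96). Over the range in step 2:

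| Outcome | Combined cohort | With 1:3 controls |
|---|---|---|
| Preterm birth, SGA | above 99.9% | above 99.9% |
| Preeclampsia | 82% to above 99.9% | 72% to above 99.9% |
| Stillbirth | 59% to above 99.9% | 49% to above 99.9% |

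**4. Would replication screen it out?** For preterm birth, the single-site probability is 68% to 100% over the whole range, and at least 96% at every site once a is 0.65 or more. For preeclampsia at a = 0.70, ρ = 0.7 it is 99%, 80%, 24%, 84% and 100% by site; the 24% belongs to the site with 7 cases. Where replication fails, it fails for lack of cases. It would fail equally often for a genuine signature of the same AUROC.

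**5. Against a clinical-only model.** Simulation, 200 runs of n = 16 221, a = 0.70, ρ = 0.7:

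| Outcome (prevalence) | Measure | Clinical only | Omics only | Clinical + omics |
|---|---|---|---|---|
| Preterm birth (0.098) | AUROC | 0.700 | 0.644 | 0.700 |
| | AUPRC | 0.2134 | 0.1649 | 0.2135 |
| Preeclampsia (0.018) | AUROC | 0.700 | 0.643 | 0.701 |
| | AUPRC | 0.0485 | 0.0341 | 0.0487 |

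The combined model was fitted and scored on the same data, so the differences in the last decimal are fitting optimism; the true gain is zero by construction. The omics-only column looks like success beside prevalence. Only the comparison of the first and last columns shows that nothing was added.

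**The case against.** The strongest reply is that this is a condensed article. Its list of metrics is not said to be exhaustive, no sentence rules out a clinical-only model, and an analysis plan that is not shown could contain one. That limits the point but does not remove it, because the article itself fixes the algorithm, resampling, metrics and acceptance rule, and makes replication the stated screen for clinical meaning.

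Three stronger readings are tempting, and the document supports none of them.

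- **That the models are judged against chance only.** Prevalence is the no-skill level of AUPRC, but the article does not call it the benchmark.
- **That an AUROC above 0.5 counts as a pass.** No cut-off is set anywhere.
- **That clinical data are added last.** The explicit sequence runs from single platform to multiple omics and from single cohort to cross-cohort. The sentence on metadata states no order.

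It is also fair to say that age, BMI and parity are adjusted for in the parallel association analyses, so a marker that only copies BMI or parity should weaken there. Blood pressure and obstetric history are not named in that list, but the list is open. This protection is not stated for the prediction models.

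Two further objections stand in part. Incremental value is not among the analytical objectives listed, and a signal that carries a BMI effect may still inform mechanism; the aims of risk assessment and prognosis nevertheless remain. The size of the effect is assumed: zero added information was put into the calculation, so it shows what the metrics cannot detect, not how likely that case is.

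**Conclusion.** The point holds as a gap in the stated evaluation. AUROC, AUPRC and prevalence, combined with replication across sites, cannot separate an omics signature that adds to clinical data from one that only reflects it. With an assumed clinical AUROC of 0.60 to 0.75 and correlation of 0.5 to 0.9, a proxy with no added information would show AUROC 0.55 to 0.73. For preterm birth it would usually replicate site by site.

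The conclusion rests on the binormal illustration only for its size. The logic needs just that some clinical risk factors act at several sites and have molecular correlates. It does not say that any MOMI signature is a proxy, and it leaves the validity of the data and of the association analyses untouched. What cannot be supported without the comparison is a claim of added predictive or clinical value.

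**What to change.** - For each outcome and pregnancy stage, also fit a clinical-only model from data available at or before the sample draw: for example age, BMI, parity, prior outcomes, enrolment blood pressure, haemoglobin, HIV status and gestational age at draw.
- For preeclampsia, leave out blood pressure readings that contribute to the outcome adjudication. Otherwise the baseline contains part of the outcome.
- Report the change in AUROC and AUPRC, clinical plus omics against clinical-only, with intervals, pooled across held-out sites and in GARBH-INi, alongside the omics-only results.
- Rest any claim of added predictive or clinical value on that pooled increment. Do not require significance at each site: with 7 preeclampsia cases at one site and 21 to 62 stillbirths per site, real gains would be lost.
- Omics-only signatures may still be reported for mechanism.

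The cost is one extra model per outcome and stage, from variables already collected, with no new assays. Headline gains may look smaller.

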### Study design

The MOMI Consortium progressed through three phases. The pre-pilot phase focused on sample quality assessment. The pilot phase was dedicated to the development and validation of the analytical workflows, while simultaneously harmonising the MOMI dataset, study outcomes, and analytical approaches [16,17,19,23,24]. The current phase (**Figure 3**) implemented population-scale molecular profiling of relevant specimens and continues with ongoing site-specific and cohort-wide data analysis and integration. Analyses are being performed on specimens collected during early (enrolment at <20 or <24 weeks GA), mid (22–28 weeks GA), and late pregnancy (28–36 weeks GA). These time points were selected to determine the dynamic trajectory of analytical factors throughout pregnancy, and test whether specific molecular signatures at one or multiple time points can predict the risk for specific APOs. Clinically, the earlier a risk for a specific APO can be identified, the higher the potential for adequate surveillance, improved clinical care, and prevention or reduced severity of the APO. Among the omics-platforms applied, metabolomics and proteomics will be applied to all longitudinal maternal specimens and cord blood, while the genomics analysis requires only a single sample from mother and infant. Maternal GARBH-INi specimens will also undergo genomics analysis. A sub-cohort study will include the longitudinal specimens of women with the most common APOs (PTB and SGA) and rare APOs (SB, very PTB, PE) plus a random sample from the full cohort (n = 5000) and 1000 women from the GARBH-INi cohort. These specimens are being analysed for nutrients group I, while in the GARBH-INi cohort, they are also being investigated for common bioanalytes and for proteomic and metabolomic APO signatures identified in the MOMI cohort. A nested case-control study (1:3) of the sub-cohort will consist of all specimens from women with rare APOs compared to women with term birth to test for biomarkers of epigenomics, nutrients of group II, and common bioanalytes. The common bioanalytes were selected based on their association with specific APOs and will only be measured at time points relevant to their role in pregnancy. Specifically, thyroid-stimulating hormone and pregnancy-associated plasma protein A will be tested in early pregnancy, whereas soluble fms-like tyrosine kinase and placental growth factor will be tested at mid and late pregnancy [25-31]. Placental tissues from a subset of women with PTB or term birth will undergo histopathology, transcriptomic, epigenomic, and global proteomic analysis.

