## DATA HARMONISATION

The Consortium has developed a harmonised framework for sociodemographic, clinical, and phenotypic variables across the biorepository sites. Specifically, SAS/STATA programmes were developed for harmonising site-specific data sets and quality control programmes for ensuring data consistency, while all harmonised datasets will be uploaded to a centralised platform. The biorepository sites upload clinical and phenotypic metadata that can be accessed by the analytical partners, who, conversely, upload their respective analytical data for cohort investigators. Although the GARBH-INi data, in compliance with government regulations in India and the GARBH-INi funding structure, are controlled by their team, data and analyses pipelines have been harmonised with the overarching MOMI Consortium. A first critical step was the harmonisation of birth outcome data, first on a site-specific level and then through central adjudication for confirmation.

PTB was defined as babies born alive before 37 weeks of pregnancy are completed [32]. Three subcategories were defined based on the GA: extremely preterm (<28 weeks, 0 days GA), (very preterm (28 weeks, 0 days to 31 weeks, 6 days GA), and moderate to late preterm (32 weeks, 0 days to 36 weeks, 6 days GA). The GA assessment was based on the Hadlock formula, which was implementable across all sites; missing head circumference data at AMANHI sites prevented the implementation of INTERGROWTH-21st formula. At time points with available ultrasound data, the GA was computed using either crown rump length or a composite of femur length and biparietal diameter. For the purpose of this study, preterm stillbirths will be evaluated as a part of SB outcomes.

SGA was defined based on the INTERGROWTH-21st standards [33] using the 10th percentile as cut-off. Only some cohort sites were able to define fifth or third percentile SGA babies. Due to discrepancies in the measurement of birth weight among the different cohort sites, birthweights were coded as level 1 or 2 when birthweights were measured within 48 or 72 hours of delivery, respectively, and as level 3 when measured at three days or later.

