SB was defined as delivery of a foetus at or after 22 weeks of gestation with no signs of life upon delivery. Among total SB cases, we classified early SB as birth prior to or at 22 weeks, 0 days to 27 weeks, 6 days of GA, and late SB when it occurred at 28 weeks, 0 days GA or later. Otherwise, SB of PTB babies were included in SB case numbers. Clinical data were used to adjudicate antepartum SB (Figure S2 in the **Online Supplementary Document**). Antepartum SB was considered priority 1 when cardiotocographic or ultrasound data of foetal death before onset of labour or rupture of membranes were available. Evidence of maceration, mummification, or other signs of putrefaction of the stillborn foetus was ascribed as priority 2 antepartum SB. An absence of perceived foetal movements as reported by the mother before the onset of labour or rupture of membranes was termed priority 3 antepartum SB.

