Due to the high cost-per-sample and medium/low sample throughput, a case-cohort study design categorised into the sub-cohort and nested case control study (**Figure 3**) was selected. The sub-cohort includes the longitudinal samples of approximately 30% of pregnant women in the full cohort and available cord blood samples for group I nutrient analysis (Figure S8 in the **Online Supplementary Document**). Nutrients of this group include vitamin A, D, E, folate, B12, total homocysteine, ferritin, transferrin receptor, iodine, minerals (copper, selenium, magnesium, calcium, phosphorus, iron, potassium, sodium), alpha-1-acid-glycoprotein, C-reactive protein, high-density lipoprotein, low-density lipoprotein, and triglycerides. It is noteworthy that the Group I Nutrient analyses will be performed by the icddr,b, representing the only in-country analysis. Group II nutrients (vitamins B1, B2, B3, B5, B6, B7, choline, and a targeted metabolomics panel) will be analysed in the longitudinal samples of PE, SB, and vPTB cases and their matched term controls (1:3 ratio). The B vitamins, choline and related metabolites will be measured by ultra-high performance liquid chromatography (UHPLC)- MS/MS and fatty acids and amino acids by UHPLC-MS/MS – MxP®Quant 500 XL kit [51,54].

As specimens of the GARBH-INi cohort will be analysed by the Translational Health Science and Technology Institute, India (THSTI), a harmonisation plan between THSTI and icddr,b, or between THSTI and UC Davis for nutrient group I or group II analyses, respectively, was developed. Institutions will apply standardised test methods, instrument calibration, quality control measures, external quality assurance schemes, and reporting methods. The joint analysis of the nutrient group I and II parameters from the GAPPS, AMANHI and GARBH-INi sites will allow for validation across sites and analytical platforms.

The placenta tissue analysis will be particularly valuable towards the goal of designing novel diagnostics or intervention strategies to prevent APOs, as several of the APOs are either entirely or partially attributable to placental dysfunction. These include early-onset PE, foetal growth restriction, and a subset of PTB cases. Since the placenta is in direct contact with maternal blood, placental APO signatures will likely be highly complementary to APO signatures in maternal blood and provide crucial information on the involvement of certain biological pathways.

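### Early delivery itself removes late samples, so the claim of bias-free handling of incomplete data cannot hold unconditionally, and machine-learning models have no stated adjustment for gestational age at sampling within a stage

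*Protocol article*

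**What the plan says.** All references are to the protocol article.

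- **Missing data** (Data analysis and data integration): imputation suited to each data type is combined with models that accept partly observed samples, "enabling inclusion of participants with incomplete data without introducing bias". No missingness assumption is given, and samples that delivery made impossible are not separated from other gaps.
- **Time points** (Study design): specimens come from early pregnancy, "mid (22–28 weeks GA), and late pregnancy (28–36 weeks GA". The aim is to "test whether specific molecular signatures at one or multiple time points can predict the risk for specific APOs".
- **Prediction models** (Data analysis and data integration): "For each outcome, a distinct model will be constructed at various pregnancy stages to capture the static risk at that time point".
- **Adjustment** (same section): "For non-machine learning association analyses, we will use a prespecified covariate framework". GA at sampling is in that list. Resampling for machine learning is stratified by site, outcome and, where relevant, case-cohort membership, but not by GA at sampling.
- **Validation** (same section): models are trained on some sites and tested on others, and only what replicates is to be read as biology.
- **Visits** (Table 1): antenatal visits after enrolment are at 22–24, 26–28, 32 and 36 weeks for GAPPS, and at 24–28, 32–36 and after 37 weeks for AMANHI.
- **Outcomes** (Data harmonisation; Table 2): very preterm birth ends before 32 weeks; the next category is "moderate to late preterm (32 weeks, 0 days to 36 weeks, 6 days GA"; early stillbirth is placed at "22 weeks, 0 days to 27 weeks, 6 days of GA".

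**The concern.** Whether a late sample exists depends on whether the woman is still pregnant, and for several of the outcomes that is the outcome itself or a close consequence of it. If such a sample is imputed, or if a model can react to its absence, information about delivery enters as if it were a molecular predictor.

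A weaker form acts even among women who were sampled. The late window is eight weeks wide, and a woman who delivers early can only be sampled early. The article's first analytical objective is to find omics signatures of each week of gestation, so the features are expected to carry GA. A model can then separate cases from non-cases partly by sampling date.

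At stake is discrimination for preterm birth, very preterm birth, stillbirth and early-onset preeclampsia that looks good but cannot be used prospectively. The plan's main protection, replication at held-out sites, does not help: delivery truncates late sampling at every site, so the artefact would replicate and be taken for biology.

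**Working it through.** **Step 1. Reproduce Table 2.** Preterm births: 223 + 384 + 366 + 372 + 242 = 1587, and 1587/16 221 = 9.78%. Very preterm births: 45 + 14 + 40 + 20 + 29 = 148, and 148/1587 = 9.33%. The preterm count and percentage and the very preterm count agree with the article; it prints no combined share for very preterm birth. It also gives no missing-data rate to reproduce.

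**Step 2. Set visits against outcomes.** Table 1 shows no scheduled GAPPS or AMANHI visit between 28 and 32 weeks. A birth before 32 weeks precedes the first scheduled late visit. An early stillbirth ends before 28 weeks and so precedes even the broad late window. Births at 32–36 weeks lose part of the window. Term births lose none of it through delivery.

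**Step 3. Assumptions** (not in the article): no biological signal; planned draw uniform over 32–36 weeks (Table 1) or 28–36 weeks (Study design); very preterm deliveries uniform over 28–32 weeks; other preterm deliveries over 32–37 weeks with density proportional to x^(k−1), where x is weeks after 32 and k runs from 1 (uniform) to 3 (strongly late); loss for unrelated reasons m from 0 to 0.38, equal in cases and non-cases. The upper m is 1 − 30 000/(3 × 16 221). It only bounds the range and does not estimate late-visit loss.

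**Step 4. Share of late samples lost to delivery, d.**

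| Window | Very preterm | Other preterm (k = 1; k = 3) | All preterm (k = 1; k = 3) |
|---|---|---|---|
| 32–36 | 1.00 | 0.40; 0.128 | 0.456; 0.209 |
| 28–36 | (36 − 30)/8 = 0.75 | 0.20; 0.064 | 0.251; 0.128 |

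For example, 0.0933 × 1 + 0.9067 × 0.40 = 0.456. In term births d = 0.

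**Step 5. AUROC of a late-sample-missing flag.** Sensitivity is d + (1 − d)m and the false-positive rate is m, so AUROC = 0.5 + 0.5 × (sensitivity − false-positive rate) = 0.5 + 0.5 × d × (1 − m).

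- Very preterm against term, 32–36: 1.00 (m = 0) to 0.5 + 0.5 × 0.62 = 0.81 (m = 0.38).
- Very preterm against term, 28–36: 0.875 down to 0.5 + 0.5 × 0.75 × 0.62 = 0.73.
- All preterm, 32–36: 0.5 + 0.5 × 0.456 = 0.73 down to 0.5 + 0.5 × 0.209 × 0.62 = 0.56.
- All preterm, 28–36: 0.63 down to 0.5 + 0.5 × 0.128 × 0.62 = 0.54.

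**Step 6. GA at sampling alone, among women sampled.** Term draws are uniform, so AUROC = (upper limit − mean GA of sampled preterm cases)/(window width).

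- 32–36: mean 33.56 (k = 1) gives 2.44/4 = 0.61; mean 33.82 (k = 3) gives 2.18/4 = 0.54.
- 28–36: mean 31.27 gives 4.73/8 = 0.59; mean 31.72 gives 4.28/8 = 0.54.

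A null simulation of 400 000 pregnancies agreed with these values to within 0.01. If absence cannot be used and GA at sampling is conditioned on, both AUROCs are 0.50 by construction.

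**The case against.** The best defence is that the missing-data sentence concerns missing omics layers or values in earlier work. Nothing in the article says that a visit that never took place will be imputed or flagged. A stage-specific late model naturally uses women who gave a late sample and were therefore undelivered, which is most of what a landmark analysis would require. Finer modelling detail may sit in a plan that is not shown.

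Much of this stands, and it rules out several stronger readings:

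- A reader might infer that the machine-learning models ignore GA altogether. They do not: modelling by stage is coarse control, and the article says elsewhere that confounding is accounted for. What is lacking is stated adjustment within a stage.
- A reader might infer that no very preterm birth can have a late sample. Table 1 gives a nominal 32-week visit for GAPPS, and Study design opens the late window at 28 weeks, so a few may have one.
- A reader might turn the figure of over 30 000 plasma samples into a missing rate. It is a lower bound, its breakdown is in a supplement not shown, and it averages over time points.
- Group II nutrients "will be analysed in the longitudinal samples of PE, SB, and vPTB cases and their matched term controls (1:3 ratio", so a reader might infer many late control assays without a case counterpart. The matching variables are not listed and the group II total is only about 1200 maternal plasma samples, so no such count follows.

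What the defence does not reach is the sentence itself, which is unconditional and introduces no exception for delivery; the plan for signatures over several time points; and the wording that ties the covariate list to non-machine-learning analyses.

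**Conclusion.** The point holds in a limited form. The article's own visit schedule and outcome definitions contradict an unconditional claim of freedom from bias, and the validation strategy on which it relies cannot reveal the problem.

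The size depends on the model. In multi-time-point or integrated models that admit women without a late sample, absence alone could yield AUROC of about 0.73–1.00 for very preterm birth and 0.54–0.73 for all preterm birth. In a late-stage model confined to women sampled, the artefact is modest: about 0.54–0.61 for preterm birth. The high values belong to very preterm birth and should not be read as applying to preterm birth in general.

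All ranges rest on the assumed timing of births and draws and on unrelated loss of 0–38%. They show what timing can produce without biology; they do not predict the trial's results. That early delivery causes the missing samples is inferred from the schedule, since the article does not discuss it. The number of early stillbirths is not given, so their contribution is not sized.

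**What to change.** 1. Delete the claim of freedom from bias, or qualify it so that it excludes samples that delivery made impossible.
2. Define each stage model, and the latest stage of any multi-time-point model, among women who at that sample are undelivered, sampled and not yet meeting the outcome definition; predict only later outcomes.
3. Do not impute samples precluded by delivery, and do not let their absence act as a predictor.
4. In the machine-learning models, adjust features for GA at sampling using the training data only, or report each model's gain over a benchmark of GA at sampling, site and clinical variables.

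This changes wording and analysis code and needs no new data. The price is fewer cases in late-stage models and a lower reported AUROC.
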